The main focus of the present paper is sociotherapy, an intervention that aims to support individuals with severe mental health disorders (i.e., schizophrenia, bipolar disorder or chronic depression). This patient-centered approach was included as a key measure in the 2017 German health care reform to improve DM and is especially relevant for psychiatric patients. As a form of structured case management, sociotherapy aims to improve coordination among healthcare providers involved in a patient’s treatment and support patients in utilizing needed healthcare services. Further goals are to foster social participation through the engagement of the patient’s social network and to offer crisis intervention if needed. In line with the Recovery Framework in mental health, the focus of sociotherapy does not lie on reducing psychiatric symptoms but rather emphasizes practical, social and daily life skills [3, 4]. Among other measures, sociotherapy ultimately aims to reduce or shorten psychiatric hospital stays [5]. Sociotherapy is typically provided by trained mental health professionals, including social workers, psychiatric nurses, and specialized therapists. Sociotherapy can be prescribed as a transitional DM measure, ideally starting immediately after discharge. To this end, an initial prescription can be issued by the hospital that lasts up to seven days, after which continued treatment requires a prescription from a licensed outpatient health care professional. In total, up to 120 sociotherapy sessions can be prescribed over a three-year period [6].

Sociotherapy as implemented in Germany shares similarities with various forms of case management found in other countries, particularly in the context of mental health care. For example, models such as Case Management (CS), Intensive Case Management, Critical Time Intervention (CTI), or Care Programme Approach (CPA) in the United Kingdom also emphasize coordinated, patient-centered care aimed at supporting individuals with severe mental illnesses [7]. Commonalities include involvement of the patient’s social network, and a focus on improving access to necessary health and social services. However, there are notable differences: the German sociotherapy framework is embedded in statutory health insurance, whereas similar programs elsewhere might operate under different funding mechanisms, timeframes or case load.

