### Confounders

In all multivariate analyses, we will adjust for key characteristics of the index event, including the PEPP category, the length of the index event, diagnoses of index event (dementia, substance abuse, schizophrenia and schizoaffective disorder, bipolar disorder and manic episodes, major depressive disorder, post-traumatic stress disorder, and personality disorder), the necessity for intensive treatment (OPS-Code 9–61), whether the admission was an emergency admission, other prescribed or certified DM measures (medication, remedies and aids, home care, outpatient intensive care specialized outpatient palliative care, patient transportation, digital health applications, and incapacity certificate). We will also control for participants' medical history prior to the index hospitalization, as such previous psychiatric hospitalizations, comorbidities in form of the Elixhauser Comorbidity Index [14] and care level. As for demographic variables, we will include age, sex, population density at the place of residence and the German Index of Socioeconomic Deprivation [15] (Table 2).

**Table 2 Tab2:** Variables

Category	Variable	Operationalization
Exposure	Sociotherapy	Prescription of Sociotherapy as a DM measure (ITT) / Prescription of Sociotherapy as a DM and utilization of at least one sociotherapy session (PPA)
Index event	PEPP	PO/PP/PA/TP/QA
	Length of index event	Number of days of index event
	Dementia	F00.x– F03.x, G30.x
	Substance abuse	F10.2, F11.2, F12.2, F13.2, F14.2, F15.2, F16.2, F17.2, F18.2, F19.2
	Schizophrenia & Schizoaffective disorder	F20.x, F21.x; F25.x
	Bipolar disorder & Manic episodes	F30.1– F30.2, F31.1– F31.2, F31.4- F31.6
	Major depressive disorder	F32.2– F32.3; F33.2– F33.3
	Post-traumatic stress disorder	F43.1
	Personality disorder	F60.x– F61.x
	Intensive treatment	OPS 9–61
	Emergency admission	Reason for admission
Discharge management measures (presciptions and certificates)	Medication	
	Remedies and aids	
	Home care	
	Outpatient intensive care	
	Specialized outpatient palliative care	
	Patient transportation	
	Digital health applications	
	Incapacity certificate	
Medical history	Elixhauser Comorbidity Index [16]	Based on all available diagnoses twelve months prior to the index event
	Number of psychiatric hospital days	Hospital stays with PEPP categories PO, PP, PA, TP & QA based on all available data twelve months prior to the index event
	Care level	Based on care level on the last day prior to the index event

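### Prior psychiatric use is coded only as total hospital days, and tobacco dependence is pooled with alcohol and drug dependence, so the balance check cannot show residual confounding from either

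*Protocol article*

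**What the plan says.** In the protocol article, the Confounders section says that all multivariate analyses will adjust for medical history, described as "previous psychiatric hospitalizations, comorbidities in form of the Elixhauser Comorbidity Index" together with care level. Table 2 then fixes how each item is measured.

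- **Prior psychiatric care** is the variable "Number of psychiatric hospital days", operationalised as "Hospital stays with PEPP categories PO, PP, PA, TP & QA based on all available data twelve months prior to the index event". The table lists no count of admissions and no time since last discharge.
- **Substance abuse** at the index event is one flag for "F10.2, F11.2, F12.2, F13.2, F14.2, F15.2, F16.2, F17.2, F18.2, F19.2". In ICD-10, F17.2 is tobacco dependence; the other codes are dependence on alcohol and other substances.
- **Major depressive disorder** is one flag for "F32.2– F32.3; F33.2– F33.3", that is, severe single and severe recurrent episodes together.
- **Comorbidity** is the Elixhauser index, "Based on all available diagnoses twelve months prior to the index event".

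Assignment procedures draws on Table 2 for the propensity score, and Analyses of primary and secondary outcomes applies the same confounders in the outcome models. Descriptives sets a standardized mean difference (SMD) below 0.1 as good balance.

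**The concern.** A propensity score balances only what is coded. If two patients with different admission patterns carry the same value, matching or weighting treats them as exchangeable on prior use, and so does the outcome model, because it uses the same list. An SMD below 0.1 for days says nothing about the number of admissions, which is not among the variables. The same holds for the mix of tobacco and other dependence inside the pooled flag.

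Past admission frequency is the natural baseline counterpart of a readmission outcome. If it also differs between patients who are and are not prescribed sociotherapy at equal total days, the estimated effect is biased. This matters most near the null. The protocol compares the intention-to-treat and per-protocol results only by sign, and its Conclusion says that a null result could reopen the question of insurance coverage. The Discussion names missing social determinants as a limitation, but not coarse coding of information that the claims do hold.

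**Working it through.** The protocol gives no figure on this point, so there is none to reproduce. The check has two parts.

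**1. Reading the text against itself.**

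- One stay of 60 days gives 60. Six stays of 10 days give 6 × 10 = 60. Table 2 assigns both patients the same value.
- The Outcomes section lists the total number of psychiatric hospitalizations and the cumulative hospital days within 365 days as separate secondary outcomes. The protocol thus accepts after discharge a distinction that it drops before the index event.
- The count can be derived: stays must be identified before their days can be summed, and the Data section gives claims from 2021 for index events from 2022.

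**2. How large could the bias be?** The documents give no associations, so every input here is an assumption. Each scenario has 1,000,000 simulated records and a true treatment odds ratio (OR) of 1. Monte Carlo error is about 0.015 on the log OR. Models within a row are fitted to the same data.

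*(a) Days against admissions.* Severity S is standard normal. Admissions are Poisson with mean exp(−0.7 + 0.7·S). Days for n admissions are gamma with shape 1.2·n and scale 20. With n capped at 5, logit P(treated) = −3 + bA·n and logit P(readmitted) = −2.4 + bY·n. Days and admissions correlate at 0.79.

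| bA / bY | Crude OR | Adjusted for days | Adjusted for log days | Adjusted for admissions | Days minus admissions |
|---|---|---|---|---|---|
| 0.1 / 0.2 | 1.023 | 1.010 | 1.008 | 1.002 | 0.008 |
| 0.2 / 0.3 | 1.062 | 1.018 | 1.016 | 0.989 | 0.029 |
| 0.3 / 0.4 | 1.181 | 1.080 | 1.076 | 1.016 | 0.064 |

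Days remove part of the confounding in every row. Taking logs changes little.

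*(b) Pooled against separate substance flags.* Tobacco and other dependence each have 25% prevalence and are independent; only the other dependence is a confounder, with the ORs shown for treatment and outcome. Intercepts are −3 and −2.2.

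| OR treatment / outcome | Crude OR | Pooled flag | Separate flags | Pooled minus separate |
|---|---|---|---|---|
| 0.7 / 1.5 | 0.992 | 1.004 | 1.019 | −0.015 |
| 0.5 / 2 | 0.927 | 0.961 | 1.014 | −0.053 |
| 1.5 / 1.5 | 1.051 | 1.035 | 1.016 | 0.019 |
| 2 / 2 | 1.110 | 1.059 | 0.996 | 0.063 |

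In the stronger scenarios the coarse coding leaves the OR about 0.04 to 0.08 away from 1. In the weaker ones the shift cannot be told from simulation noise or is very small. The direction follows the assumed associations.

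**The case against.** The best defence is that the prose names a concept, Table 2 operationalises it, and days are a legitimate summary. The list also holds PEPP category, length of the index event, intensive treatment, emergency admission, care level, other diagnoses and the Elixhauser index, which may absorb much of what an admission count would add. This stands in part: it limits the likely size, and the prose and table differ in precision without flatly contradicting each other. It does not explain why the quantity closest to the outcome is left out when it can be built from the same records.

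A reader might infer more than the documents support.

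- **That confounding is certainly left.** Nothing shows that these distinctions predict both prescription and readmission once the other covariates are in.
- **That frequent readmission triggers the prescription.** The Background gives target conditions and aims, but no such trigger.
- **That the substance flag mostly marks smokers.** It is built from diagnoses of the index event, and no code frequencies are given.
- **That the bias is large.** A hand example with equal prior days, frequent admitters at 50% of treated and 30% of controls, and risks of 20% and 10% gives 0.15 / 0.13 = 1.15. That rests on an assumed 20-point imbalance and ignores every other covariate. Similarly, within the substance flag, take non-tobacco dependence in 30% of treated and 60% of controls, with risks of 15% and 10%. The risks are then 0.115 and 0.13, a ratio of 0.88, but only among flagged patients. If 30% of each arm is flagged and unflagged risk is 10%, the overall ratio is (0.3 × 0.115 + 0.7 × 0.10) / (0.3 × 0.13 + 0.7 × 0.10) = 0.1045 / 0.109 = 0.96.
- **That splitting F32 from F33 would capture the indication.** The Background names "schizophrenia, bipolar disorder or chronic depression"; recurrent is not the same as chronic, and a single episode can be long.

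**Conclusion.** The point holds as a risk of residual confounding from two stated coding choices: prior psychiatric use as days only, and tobacco dependence inside the pooled substance flag. Because Table 2 fixes both definitions, this is not a matter of detail left to another document. The planned SMD check cannot detect the problem, since the finer variables are not coded.

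Size and direction cannot be determined from the documents. On assumed inputs the residual distortion runs from negligible to about 0.04 to 0.08 on the OR, upward or downward. That justifies an inexpensive improvement made before analysis; it does not invalidate the design. Pooling single with recurrent severe depression is a weaker point and supports an optional refinement only.

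**What to change.** 1. Add the number of psychiatric admissions in the twelve months before the index event to Table 2, alongside days, and use it in the propensity score, the outcome models and the SMD balance table. Count episodes with the same-day transfer rule already given under Outcomes, so that a transfer is not counted as a new admission.
2. Take F17.2 out of the pooled substance flag, giving it its own indicator or dropping it.
3. Align the Confounders wording with Table 2 so that both name the same quantities.

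Optional: time since last psychiatric discharge, in categories that include none within twelve months, because it is otherwise undefined for patients without a prior stay; and separate flags for F32.2–F32.3 and F33.2–F33.3, without presenting that split as a measure of chronicity.

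The stays and codes are already in the planned data. The cost is a few more propensity-model terms, which matters only if the treated group is small. The protocol itself allows that the required sample may not be reached; in that case the admission count should come first and the optional terms can be left out.

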## Discussion

By employing the TTE framework, we adopt a systematic approach that minimizes the risk of bias when analyzing real-world data, thereby enhancing the reliability and validity of our findings. If feasible, our study will be among the first to provide robust evidence on the effectiveness of sociotherapy for reducing readmission rates among psychiatric inpatients. However, the insurance claims data used in this study provide limited and potentially less reliable information on key social determinants, such as social support, family or employment status. As a result, we are unable to account for these potential confounders, which may influence the primary and secondary outcomes. Furthermore, the reduction in psychiatric readmissions or the shortening of psychiatric hospital stays are not the only potential benefits of sociotherapy. Our study does not evaluate the impact of sociotherapy impact on the utilization of outpatient healthcare services and better coordination between healthcare providers, nor does it consider broader outcomes such as patient motivation, social participation, or the engagement of the patient’s social network, all of which are key goals of sociotherapy.

## Conclusion

In conclusion, our study aims to provide robust evidence regarding the effectiveness of sociotherapy prescriptions as a DM component on psychiatric readmissions. By employing the TTE framework, we aim to minimize bias and enhance the reliability of our findings which are derived from real-world data. The study addresses a critical lack of evidence for a treatment which is codified in German law and covered by German health insurances. If sociotherapy proves to be effective on the reduction of psychiatric readmissions, the findings could support its broader implementation and integration into routine care. Conversely, if no significant effect is observed, the results could spark a renewed discussion about the treatment’s role and barriers—ranging from exploring other potential beneficial outcomes, such as improved social participation and patient engagement, exploring potential barriers of implementation especially in regard to a fast provision after hospital discharge versus long, bureaucratic processes, to reconsidering its inclusion in health insurance coverage.

## Data Availability

No datasets were generated or analyzed during the current study.

## Abbreviations

DM: Discharge Management
GKV: National Association of Statutory Health Insurance Funds
KBV: National Association of Statutory Health Insurance Physicians
DKG: German Hospital Federation
CS: Case Management
CTI: Critical Time Intervention
CPA: Care Programme Approach
TTE: Target Trial Emulation
RCT: Randomized Controlled Trials
TK: Techniker Krankenkasse
PEPP: Psychiatric and Psychosomatic Compensation System
PSM: Propensity Score Matching
IPW: Inverse Probability Weighting
ATT: Average Treatment Effect Among the Treated
ITT: Intention-to-Treat Analysis
PPA: Per-Protocol Analysis
SMD: Standardized Mean Difference
NUTS: Nomenclature des Unités territoriales statistiques
